## Abstract

**Introduction:**

Cognitive behavioural therapy for psychosis (CBTp) has demonstrated effectiveness in reducing positive symptoms, improving depression, enhancing coping skills and increasing awareness of illness. However, compared with cognitive behavioural therapy for depression and anxiety, the spread of CBTp in clinical practice is minimal. The present study designed a randomised controlled trial (RCT) research protocol to evaluate whether real-time remote video-conference CBTp (vCBTp) could facilitate access to psychosocial interventions and effectively improve symptoms compared with usual care (UC) for patients with schizophrenia.

**Methods and analysis:**

This exploratory RCT will consist of two parallel groups (vCBTp+UC and UC alone) of 12 participants (n=24) diagnosed with schizophrenia, schizoaffective disorder or paranoid disorder, who remain symptomatic following pharmacotherapy. Seven 50-min weekly vCBTp interventions will be administered to test efficacy. The primary outcome will be the positive and negative syndrome scale score at week 8. The secondary outcome will be the Beck Cognitive Insight Scale to assess insight, the Patient Health Questionnaire-9 to assess depression, the Generalised Anxiety Disorder-7 to assess anxiety, the 5-level EuroQol 5-dimensional questionnaire to assess quality of life and the Impact of Event Scale-Revised to assess subjective distress about a specific stressful life event. We will take all measurements at 0 weeks (baseline) and at 8 weeks (post-intervention), and apply intention-to-treat analysis.

**Ethics and dissemination:**

We will conduct this study in the outpatient department of Cognitive Behavioral Therapy Center at Chiba University Hospital. Further, all participants will be informed of the study and will be asked to sign consent forms. We will report according to the Consolidated Standards of Reporting Trials.

**Trial registration number:**

UMIN000043396.

Strengths and limitations of this studyThis study will be a pilot randomised controlled trial to test the effectiveness of real-time remote cognitive behavioural therapy using a video-conference system for outpatients diagnosed with schizophrenia.The intervention comprises seven sessions, with elements of psychoeducation, case formulation and cognitive restructuring.Remote cognitive behavioural therapy in this study has the potential to reduce the burden of access for receiving cognitive behavioural therapy for schizophrenia.This is a single-centre pilot study and statistical analysis between the usual care (UC) and video-conference cognitive behavioural therapy for psychosis+UC groups will be limited to exploratory comparisons.

## Introduction

Based on the fifth edition of the Diagnostic and Statistical Manual of Mental Disorders (DSM-5), schizophrenia is a mental disorder associated with functional disability, poor quality of life and early death.^1^ Schizophrenia is a severe, lifelong mental disorder that affects approximately 1% of the world’s population.^2^ The illness tends to develop between the ages of 16 and 30 years.^3^ Individuals with schizophrenia use a substantial amount of healthcare services. This condition imposes a significant economic burden on both the patients and their families, and on society as a whole.^4^

### Standard treatment for schizophrenia

The treatment of schizophrenia is multidimensional and comprehensive. The first treatment option is pharmacotherapy with antipsychotic medications and psychological interventions such as cognitive-behavioural therapy, as recommended by the National Institute of Health and Clinical Excellence.^5^ Antipsychotic medications are commonly used for patients with schizophrenia primarily to reduce positive symptoms such as hallucinations and delusions by regulating the activity of dopamine and other nerves in the brain. In recent years, atypical antipsychotic prescriptions have been promoted. They effectively improve positive and negative symptoms and cognitive function but may cause side effects in some patients.

The American Psychiatric Association guidelines^6^ and the Schizophrenia Patient Outcomes Research Team^7^ recommend psychosocial interventions in combination with pharmacotherapy. Comprehensive treatment measures include individual and group psychotherapy, psychoeducation, occupational therapy, family therapy and psychosocial interventions such as social skills training.^8^

### Cognitive behavioural therapy for schizophrenia

Cognitive behavioural therapy for psychosis (CBTp) has been shown to reduce positive symptoms and improve coping skills in Europe and the USA.^9^ Kuller *et al*^10^ reported that CBTp is used in 58% of US medical facilities and 91.3% of UK medical facilities. Wykes *et al*^11^ reported an effect size of 0.40 (0.25–0.55) in a meta-analysis of 33 randomised controlled trials (RCTs) (n=1964) on CBTp. Jauhar *et al*^12^ found an effect size of 0.33 for general symptoms in a meta-analysis of 34 studies on CBTp for schizophrenia. The National Institute of Health and Clinical Excellence recommends a session structure of 16 sessions or more.^5^ However, despite the evidence, the number of practitioners is insufficient; thus, it is challenging for patients to access CBTp.^13^ Additionally, CBTp is important because patients’ characteristics and problems are diverse due to the illness’s nature. It is essential to be flexible in dealing with mood and thoughts, realistic and rational thoughts and delusional and pathological experiences.^14^

There are reports of an association between intrusive thoughts of post-traumatic experiences and schizophrenia.^15 16^ There is also a discussion of the potential for CBTp to address intrusive thoughts.^17^

In the future, it will be desirable to establish an effective implementation system for CBTp and increase the number of practitioners in clinical practice.

Evidence of low-intensity CBTp has been collected overseas and its effectiveness has been recognised too.^18 19^ Turkington *et al*^20 21^ found that community psychiatric nurses’ provision of low-intensity CBTp, comprising six sessions, effectively increased awareness of the illness. Overall, six sessions of a 6-week low-intensity CBTp provided by community psychiatric nurses improved the understanding of illness, general status and depression. This suggests that CBTp offered by healthcare professionals may also be effective. Recently, studies have begun investigating CBTp that can be effectively administered online using the internet.^22–25^

#### Video-conference cognitive behavioural therapy for psychosis

The number of CBTp practitioners is limited and their use in clinical practice is much less frequent. As a remedy to this problem, there is growing interest in using video-conferenced systems to provide CBT, known as vCBT.^26^ This approach has the advantage of providing access to CBT for patients living in remote areas and enabling remote treatment through interactive, real-time communication between the therapist and patient.^27^ Although therapist-guided internet-based CBT is shown to be not inferior to face-to-face CBT in treating anxiety, depression, insomnia and somatic disorders,^28^ there are less reports about internet-based CBTp. Up to this point in 2022, to the best of our knowledge, no studies have examined the efficacy of individual CBTp using a video-conference system (vCBTp) for schizophrenia.^29^

### Objective

This article describes the study protocol of a RCT designed to evaluate the clinical efficacy of seven sessions of vCBTp, as an adjunct to usual care (UC) compared with UC alone. The trial focuses on patients with schizophrenia who continue experiencing positive symptoms despite receiving pharmacotherapy.

## Methods and analysis

### Study design

The study is designed as a single centre, assessor-blind, two-arm, parallel, prospective, randomised, controlled trial comprising a 7-week treatment regimen. Participants will be allocated to vCBTp plus UC or UC alone (figure 1). We will report according to the Consolidated Standards of Reporting Trials (CONSORT) and the Standard Protocol Items: Recommendations for Interventional Trials reporting guidelines.^30^

**Figure 1 F1:**
[figure not shown]
Flow chart. CONSORT patients’ flow diagram of the study, randomisation and treatment. CBT, cognitive behavioural therapy; CONSORT, Consolidated Standards of Reporting Trials.

### Details of recruitment

The researchers will recruit participants through websites, posters and leaflets placed at medical institutions in Chiba prefecture, Japan, from April 2021 to March 2025 until 24 participants will be enrolled. Participants will be required to obtain permission from their psychiatrists before enrolment in the study and continue to receive medical care including pharmacotherapy from their psychiatrists. The study will be conducted in the Cognitive Behavioural Therapy Center outpatient clinic at Chiba University Hospital.

### Intervention methods

Participants will not be restricted to changes in their medications by their psychiatrists during the study period. If clinically appropriate, they will be allowed to participate in usual psychosocial intervention programmes such as social skills training at psychiatric daycare or night care.

However, to properly evaluate the effectiveness of vCBTp, participants may not receive other CBT or specific psychotherapies including psychoanalytical therapy, Morita therapy, insight therapy, hypnotherapy, brain stimulation therapies including electroconvulsive therapy or magnetic stimulation therapies. The vCBTp+UC group will receive the text material developed by the research team by mail. All seven sessions will be conducted according to the text material. The therapist will assign homework to the participants at the end of each session, as described in the text material.

### Outcomes

#### Baseline and clinical characteristics

The baseline and clinical characteristics included sex, age, marital status, employment status, age at onset of schizophrenia, duration of illness and treatment history including the name of the antipsychotic to which the patient has developed resistance, current drug titres at baseline, and any changes in conventional treatment during the study period will be collected by researchers.

#### Secondary outcomes

The secondary outcomes are the following:

We will evaluate the sum of positive symptoms, negative symptoms and general psychopathology extracted from the PANSS subscales score, respectively. The total score of the seven positive symptoms subscale on the PANSS ranges from 7 (no symptoms) to 49 (severe positive symptoms). The total score of the seven negative symptoms subscale ranges from 7 (no symptoms) to 49 (severe negative symptoms). The total score of the 16 items of general psychopathology subscale ranged from 16 (no symptoms) to 112 (severity of psychopathology).

The Japanese version of the Beck Cognitive Insight Scale (BCIS-J)^36^ will be used to assess cognitive insight. A total of 15 items of the BCIS-J are divided into 9 items of self-reflection (0–36) and 6 items of self-confidence (0–24). The lower the subtotal of 9 self-reflection items minus 6 self-confidence items, the lower the cognitive pathology.

The Impact of Event Scale-Revised (IES-R)^37^ will be used to assess subjective distress for a specific stressful life event. The 22 items (0–88) of IES-R comprise eight intrusive symptoms, eight avoidance symptoms and six hyperarousal symptoms, and can measure symptoms in persons exposed to traumatic experiences.

The PHQ-9^38^ will be used to assess depressive symptoms. PHQ-9 comprises nine items ranging from 0 (no depressive symptoms) to 27 (severe depressive symptoms).

The Generalised Anxiety Disorder-7 (GAD-7)^39^ will be used to assess anxiety. GAD-7 comprises seven items ranging from 0 (no anxiety symptoms) to 21 (severe anxiety symptoms).

The 5-level EuroQol 5-dimensional questionnaire^40^ will be used to assess quality of life. It comprises five items and assesses the quality of life on a 5-point Likert scale from 1 (not severe) to 5 (severe). It is the most commonly used measure of quality-adjusted life-years worldwide.

In addition, we will evaluate the chlorpromazine equivalent to daily prescriptions for antipsychotic medications.^41^

Therapists will ask the participants about their experience of adverse events during each assessment. All measures will be assessed at week 0 (baseline) and week 8 (post-intervention), and the results will be analysed per the intention-to-treat principle.

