### Data analysis plan

The study will follow the CONSORT guidelines for statistical analysis and reporting. The primary analysis will be based on the intention-to-treat principle. To evaluate the primary outcome, the changes in the PANSS total score at week 8 will be calculated for both the UC group and the vCBTp+UC group. A comparison between the groups will be performed using an unpaired t-test. Secondary outcomes will also be analysed to provide further understanding of the primary endpoints, following a similar approach as the primary outcome analysis. In addition, the number of subjects in each group who have improved by 20% of the total PANSS score are considered to be treatment-responsive and the proportion of subjects in each group is calculated. The χ^2^ test is used to compare proportions between groups. The safety endpoint is the frequency of adverse events, and a tabulation table is prepared for the endpoints with exact two-sided 95% CIs of the binomial distribution calculated for each group for percentage estimates. If necessary, a comparison between groups is made using the Fisher’s direct probability calculation method. The statistical analyses will be performed using SAS V.9.4 (SAS Institute, Cary, North Carolina, USA), and a p value of <0.05 will be considered statistically significant.

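### The stated reading of the BCIS-J index (lower means less pathology) contradicts its use as a measure of cognitive insight

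*Protocol article*

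**What the plan says.** The abstract lists, among the secondary outcomes, "the Beck Cognitive Insight Scale to assess insight". The Secondary outcomes section says that the BCIS-J "will be used to assess cognitive insight". It splits the 15 items into nine for self-reflection, scored 0 to 36, and six for self-confidence, scored 0 to 24. The index is the first subtotal minus the second. The section then gives the reading: "The lower the subtotal of 9 self-reflection items minus 6 self-confidence items, the lower the cognitive pathology".

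The Data analysis plan handles secondary outcomes by "following a similar approach as the primary outcome analysis". For the primary outcome, that approach is the change at week 8 in each arm, and "A comparison between the groups will be performed using an unpaired t-test". No direction for the BCIS-J is given anywhere else in the article.

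**The concern.** The sentence fixes which way the index must move to count as benefit, and it appears to fix it the wrong way. An index that adds self-reflection, on a scale meant to capture insight, should rise as insight rises. The article says instead that the low end is the healthy end.

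What is at stake is how one secondary outcome is interpreted. If vCBTp increased self-reflection, an author or table programmer following this sentence would describe the change as a deterioration, and a fall would be described as a gain. A two-sided test would not expose the slip, because significance is the same whichever way the result is read. The slip is also easy to carry forward. The PANSS subscales, the PHQ-9 and the GAD-7 are all described in the same section as running from no symptoms upwards, so a single convention that a decrease is an improvement would take in the BCIS-J without anyone noticing.

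**Working it through.** The article gives no numerical result for this scale to reproduce. The check concerns the sign of the index and where the direction enters the analysis.

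**Inputs (Secondary outcomes section).** Self-reflection SR runs from 0 to 36 (nine items) and self-confidence SC from 0 to 24 (six items). Index I = SR − SC.

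**Range of the index.**
- Lowest value: SR = 0 and SC = 24 give I = 0 − 24 = −24.
- Highest value: SR = 36 and SC = 0 give I = 36 − 0 = +36.

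**What the stated rule implies.** Lower I means lower pathology. So −24, with no self-reflection at all, is the least pathological score possible, and +36, with full self-reflection, is the most pathological.

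**Self-reflection alone.** Hold SC fixed and raise SR by 1, and I rises by 1. By the stated rule, that participant now has more cognitive pathology. By the stated purpose of the scale, a participant who scores higher on the component that is added has more cognitive insight. The two statements agree only if more insight means more pathology, and the article nowhere says that. This step needs no view on whether self-confidence is good or bad.

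**An illustrative participant (values chosen for the example).**
- Baseline: SR = 12, SC = 10, I = 12 − 10 = 2.
- Week 8: SR = 15, SC = 8, I = 15 − 8 = 7.
- Change: 7 − 2 = +5.

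Read as insight, +5 is an improvement. Read by the stated sentence, the same +5 is a worsening.

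**Where the direction enters the analysis.** The between-group estimate is D = (mean change in I, vCBTp+UC) − (mean change in I, UC). The unpaired t-test and the confidence interval are computed from D and the standard deviations of the changes. The sentence on pathology appears in none of these. The test is not one-sided, there is no margin, and there is no BCIS-J responder cut-off; the only responder rule in the Data analysis plan is on the PANSS total. So D, its interval and the two-sided p value are the same under either reading. Only the label of benefit or harm attached to D changes.

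**Other statements in the article.** The abstract counts among the benefits of CBTp "enhancing coping skills and increasing awareness of illness". The introduction reports that a six-session low-intensity programme "improved the understanding of illness, general status and depression". Both treat greater awareness or understanding as good. They concern illness, however, and not cognitive insight by name, so they lend only loose support.

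**The case against.** The best defence is that this is one descriptive sentence about an instrument in a condensed article, quite possibly a slip of wording or translation, and that an analyst who knows the scale would not follow it. That is fair as to likelihood, and it makes the harm conditional. It does not remove the contradiction: the article chose to state a direction, and nothing in it puts the direction right.

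A second argument is that the correct direction cannot be settled without the scale's manual, since the article never says that more self-confidence is undesirable. This stands in part. To read the self-confidence items as overconfidence, or as rigid certainty in one's own beliefs, is an inference that the text does not make. The contradiction holds on the self-reflection term alone, but the fix should still include a check against the cited Japanese scale.

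Three stronger readings may tempt a reader, and the document does not support them:
- **That the estimated effect would be reversed.** It would not. The formula for the index is fixed, and D, its interval and the p value follow from it whatever the sentence says.
- **That the error undermines the benefit claimed for CBTp on awareness of illness.** The article does not equate awareness of illness with what the BCIS-J measures.
- **That the item ranges are also wrong.** The stated ranges agree with each other: 36/9 = 4 and 24/6 = 4, so each item has a maximum of 4 in both parts. Nothing in the article calls them into question.

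**Conclusion.** The point holds as an error in a stated rule of interpretation. The article names the BCIS-J as a measure of cognitive insight, builds an index that rises with self-reflection, and then says that a lower index is the less pathological one.

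The consequence is limited to the reading of one secondary outcome: taken literally, every rise in the index on vCBTp would be labelled harm and every fall benefit. The computed difference, its confidence interval and the two-sided p value are unaffected, as are the primary PANSS comparison and the sample size. The trial is also a 24-participant pilot whose between-group analyses are described as exploratory. The scale is nevertheless the first secondary outcome named in the abstract, and the Discussion makes a larger study depend on some sign of efficacy, so the direction should be right before results are tabulated.

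The conclusion rests on two assumptions: that a higher self-reflection score on an insight scale means more insight, and that the sentence would be applied as written. The first follows from the article's own description of the scale; the second may not come to pass.

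**What to change.** Replace the sentence so that a higher value of self-reflection minus self-confidence means greater cognitive insight, and improvement is a positive change from baseline. Before making the change, confirm this direction against the cited Japanese version of the scale. State the direction of benefit beside the BCIS-J in the results tables, so that it is not swept into a convention under which a decrease is an improvement.

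The cost is one sentence, one look at the scale's source and one table label. No data collection, test or sample size changes.

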### Sample size

Primarily, this study aims to test the superiority of vCBTp on symptom improvement in a group of patients with schizophrenia compared with a UC group. We refer to a previous study by Morrison *et al*^42^ in which CBT and antipsychotic groups were compared. Assuming that the mean difference between the vCBTp plus UC group and UC alone group after the intervention is 12 points and the SD of the pooled UC group is 8, the number of patients in each group was calculated as 11 for a significance level of 5% on both sides and a power of 90%. Therefore, the target number of patients was set at 12 in each group, assuming a dropout rate of 10% for 24 patients. Furthermore, a previous study suggested that 12 patients in each group is an appropriate number in a pilot study.^43^

### Data analysis plan

The study will follow the CONSORT guidelines for statistical analysis and reporting. The primary analysis will be based on the intention-to-treat principle. To evaluate the primary outcome, the changes in the PANSS total score at week 8 will be calculated for both the UC group and the vCBTp+UC group. A comparison between the groups will be performed using an unpaired t-test. Secondary outcomes will also be analysed to provide further understanding of the primary endpoints, following a similar approach as the primary outcome analysis. In addition, the number of subjects in each group who have improved by 20% of the total PANSS score are considered to be treatment-responsive and the proportion of subjects in each group is calculated. The χ^2^ test is used to compare proportions between groups. The safety endpoint is the frequency of adverse events, and a tabulation table is prepared for the endpoints with exact two-sided 95% CIs of the binomial distribution calculated for each group for percentage estimates. If necessary, a comparison between groups is made using the Fisher’s direct probability calculation method. The statistical analyses will be performed using SAS V.9.4 (SAS Institute, Cary, North Carolina, USA), and a p value of <0.05 will be considered statistically significant.

